## Abstract

**Background:**

Asthma is a common disease characterized by chronic inflammation of the lower airways, bronchial hyperactivity, and (reversible) airway obstruction. The Global Initiative of Asthma Guideline recommends a flowchart to diagnose asthma with first-step spirometry with reversibility and a bronchial challenge test (BPT) with histamine or methacholine as a second step [1]. The BPT is considered burdensome, time-consuming for patients and staff, can cause side effects, and is expensive. In addition, this test strongly encumbers lung function capacity. Elevated Nitric Oxide (NO) is associated with airway eosinophilic inflammation in asthma patients and can be measured in exhaled air with the Fractional exhaled (Fe) NO-test. This low-burden FeNO-test could be used as an ‘add-on’ test in asthma diagnostics [2, 3].

**Methods and analysis:**

This multi-center prospective study (Trial number: NCT06230458) compares the ‘standard asthma diagnostic work-up’ (spirometry with reversibility and BPT) to the ‘new asthma diagnostics work-up’ (FeNO-test as an intermediate step between the spirometry with reversibility and the BPT), intending to determine the impact of the FeNO-based strategy, in terms of the number of avoided BPTs, cost-effectiveness and reduced burden to the patient and health care. The cost reduction of incorporating the FeNO-test in the new diagnostic algorithm will be established by the number of theoretically avoided BPT. The decrease in burden will be studied by calculating differences in the Visual Analogue Scale (VAS) -score and Asthma Quality of Life Questionnaire (AQLQ) -score after the BPT and FeNO-test with an independent T-test. The accuracy of the FeNO-test will be calculated by comparing the FeNO-test outcomes to the (gold standard) BPTs outcomes in terms of sensitivity and specificity. The intention is to include 171 patients.

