### Study design

The study starts with a standard care visit in which all patient characteristics are collected. During this visit, blood will be collected to measure total IgE (tIgE), specific IgE (sIgE) to inhalation allergens, and eosinophils to map the asthma profile of the patient. After that, all patients undergo spirometry with reversibility. If there is no reversibility, the patient will ask to participate in the study.

In a separate appointment, the BPT test (standard care) and FeNO-test (extra) will be done, and the diagnostic burden will be measured (Visual Analogue Scale (VAS)) after each test. After the study visit, the patient will receive the results of the FeNO-test and the BPT and will be treated.

if they are diagnosed with asthma or get extra investigations if there is no asthma (standard care 2). After 3 months, patients will be medically controlled by the pulmonary physician for evaluating treatments and quality of life with the Asthma Control Questionnaire (ACQ) and Asthma Quality of Life (AQLQ) (standard consult 3, digital consult), and 2 additional questionnaires will be administered. The study program and diagnostic results are shown in Table 1; Fig. 1.

**Table 1 Tab1:** Study program

Standard care 1.	• Consult pulmonary physician • Blood testing • Spirometry
**Study visit 1**	• BPT (standard care) • Informed consent • FeNO-test (extra) • Questionnaires (VAS) (2, extra)
Standard care 2.	• Results of the FeNO-test and BPT • Diagnosis • Possible treatment • Possible additional investigations
Standard care 3.	• ACQ, AQLQ after 3 months of treatment (digital consult)

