### Statistical analysis

Patient- and study characteristics will be reported in percentages, means, and standard deviation. The cost reduction of incorporating the FeNO-test in the new diagnostic algorithm will be established by the number of theoretically avoided BPT, theoretically avoided days of absenteeism caused by the BPT, and extra FeNO measurements. The decrease in burden will be studied by calculating differences in VAS-score and AQLQ-score after the BPT and FeNO-test with an independent T-test. The mean delta ACQ after 3 months of treatment in the patients with asthma and without asthma will be determined and also compared with an independent T-test. The accuracy of the FeNO-test will be calculated by comparing the FeNO-test outcomes to the (gold standard) BPTs outcomes in terms of sensitivity and specificity. A p-value of 0.05 will be considered statistically significant. The post-hoc analysis will be performed for subgroups of the patients; smokers and obese patients.

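### The planned burden comparison of AQLQ between the BPT and the FeNO-test cannot be estimated, because the published schedule attaches no AQLQ score to either test

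*Protocol article*

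**What the plan says.** The Abstract (Methods and analysis) names two measures of the decrease in burden, the VAS and the "Asthma Quality of Life Questionnaire (AQLQ) -score after the BPT and FeNO-test with an independent T-test". The Statistical analysis section says the same: "The decrease in burden will be studied by calculating differences in VAS-score and AQLQ-score", with the comparison made between the two tests by an independent t-test.

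Study design sets out when each instrument is used. On the tests: "In a separate appointment, the BPT test (standard care) and FeNO-test (extra) will be done". On burden: "the diagnostic burden will be measured (Visual Analogue Scale (VAS)) after each test". Table 1 agrees, listing "Questionnaires (VAS) (2, extra" at study visit 1 and no AQLQ there. The AQLQ appears in Table 1 only under standard care 3: "ACQ, AQLQ after 3 months of treatment (digital consult". The text gives the purpose of that consult as "evaluating treatments and quality of life with the Asthma Control Questionnaire (ACQ) and Asthma Quality of Life (AQLQ", which concerns treatment and quality of life rather than how burdensome a test was.

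The Outcomes section treats patient burden in one sentence and asthma control and quality of life, by group, in another.

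**The concern.** A comparison of burden between two tests needs either a score for each test from the same patient, or separate groups of patients who had only one test. The VAS meets the first condition. On the published schedule the AQLQ meets neither: it comes about 3 months after both tests, and no group had the BPT alone or the FeNO-test alone.

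Reduced burden on the patient is one of the study's headline aims and part of its stated case for changing the asthma guidelines. If one of its two named measures cannot be produced, whoever runs the analysis must either drop it without explanation or put something else in its place. A split of the 3-month AQLQ by FeNO or BPT result, for example, would compare disease status and treatment and would say nothing about test burden.

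**Working it through.** The plan gives no figure for this comparison, so the check sets the planned analysis against the assessment schedule.

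**Step 1: what each instrument yields per patient** (Study design and Table 1)

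| | VAS | AQLQ |
|---|---|---|
| After the BPT | 1 | none listed |
| After the FeNO-test | 1 | none listed |
| 3-month consult | none listed | 1 |
| Scores belonging to one test | 2 | 0 |

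With the intended 171 patients, that is 171 × 2 = 342 VAS scores, each tied to a test, and 171 × 1 = 171 listed AQLQ scores, none tied to a test.

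**Step 2: the within-patient contrast.** For patient *i*, the VAS difference is VAS(BPT) − VAS(FeNO), and both terms exist. The AQLQ difference would be AQLQ(BPT) − AQLQ(FeNO), and neither term exists. If the single 3-month score A is assigned to both tests, the difference is A − A = 0 for every patient whatever the data. Running the independent t-test on 171 simulated scores entered twice gave t = 0 and p = 1.

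**Step 3: the between-group contrast.** An independent t-test would need a BPT group and a FeNO group. Every participant has both tests, so both groups are empty. Grouping by test *result* is possible, but that is not grouping by test *undergone*.

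**Step 4: would a baseline AQLQ help?** The change from baseline to 3 months is again one number per patient and again follows both tests. Assigned to both, it also differs by 0. A baseline score could sharpen a comparison of diagnostic groups, but it cannot separate the tests.

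**Step 5: do other statements supply the missing scores?**
- Study design mentions two additional questionnaires, in the sentence on the 3-month consult, and does not name them.
- Ethics and dissemination places questionnaires after each test and at 3 months and names no instrument. Table 1 names the VAS for the test visit.
- Outcomes refers to quality of life in different groups, which supports a comparison of groups of patients and not of tests.

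**Step 6: is the sample size touched?** It rests on the share of avoidable BPTs: 0.39 × 0.60 + 0.61 × 0.15 = 0.3255. With a 95% interval of total width 0.15 (half-width 0.075), N = 1.96² × p(1 − p) / 0.075². This gives 149.94, so 150, at 32.55%; 95.91, so 96, at 16.9%; and 170.69, so 171, at 49.2%. All three match Sample size calculation, and the AQLQ plays no part in them.

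**The case against.** The strongest reply is that the article is condensed and its schedule visibly incomplete. The Statistical analysis section plans a change in ACQ after 3 months, which needs an earlier ACQ, yet Table 1 lists the ACQ only at 3 months. Some questionnaires are unnamed, and Fig. 1 is not available here. A reader might infer from Table 1 that each patient completes the AQLQ only once in the whole study. The documents do not establish that: it holds for the schedule as published, and an unlisted baseline AQLQ is possible. This part of the reply stands. It does not rescue the analysis, because a baseline score would not attach to either test (Step 4), and both the text and Table 1 name the VAS alone after each test.

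A second reply is that two analyses were merged into one sentence: VAS between tests, and AQLQ between patients with and without asthma, as is planned for the ACQ. An independent t-test would suit the latter, and Outcomes does keep the two topics apart. This is plausible and points to the repair. The sentence as written, in both places, still makes AQLQ a measure of the difference in burden between tests.

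A reader might also infer that the sponsor intends to present AQLQ by FeNO result as a burden finding. No such split is planned, so this is a risk left open by the wording and not something the plan states.

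**Conclusion.** The AQLQ part of the burden comparison is wrong as written. The published schedule attaches no AQLQ score to the BPT or to the FeNO-test, so the between-test contrast is not estimable, and neither a paired nor an independent test would change that. The loss is one of two named burden measures.

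The conclusion rests on two points that the text and Table 1 agree on: all participants have both tests at one appointment, and the VAS is the only instrument named after each. It does not depend on whether a baseline AQLQ exists. It would change only if an AQLQ were in fact taken separately for each test, which nothing in the article indicates.

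A reader might conclude that the burden aim, or the study's main result, fails. The document does not support that. The VAS measures burden directly after each test, and the avoided-BPT, cost and accuracy outcomes and the sample size do not use the AQLQ. The severity is moderate.

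**What to change.** 1. In the Abstract and in Statistical analysis, remove AQLQ from the comparison between the BPT and the FeNO-test.
2. State that test burden rests on the two VAS scores per patient. As these come from the same patient, the independent t-test named in that sentence does not suit them. This is a separate matter, but the rewritten sentence should name a paired analysis.
3. Report the 3-month AQLQ by diagnostic group, in line with Outcomes, and say that it is not interpreted as test burden. Adjust for baseline only if a baseline AQLQ is already collected; otherwise adjustment would require an assessment that the schedule does not list.

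The cost is a change of wording and one fewer claimed burden measure. No new data are needed, and the sample size stays as it is.

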**Ethics and dissemination:**

The local medical ethics committee approved the proposed study and is considered a low-burden and risk-low study. The local medical ethics committee registration number: R23.005.

**Strengths and limitations of this study:**

Strengths: This is the first study that investigates the value of the FeNO-test (cut off ≥ 50 ppb) as an add-on test, to determine the impact of the FeNO-based strategy, in terms of the number of avoided BPTs, cost-effectiveness, and reduced burden on the patient and health care. Limitations: High FeNO levels may also be observed in other diseases such as eosinophilic chronic bronchitis and allergic rhinitis. The FeNO-test can be used to rule in a diagnosis of asthma with confidence, however, due to the poor sensitivity it is not suitable to rule out asthma.

**Supplementary Information:**

The online version contains supplementary material available at 10.1186/s12890-024-02990-2.

## Background

Asthma is a common disease with an increase in prevalence worldwide [4]. Diagnosing asthma in time (early recognition) is relevant to prevent deterioration of the lungs and to be able to treat the patient adequately.

The GINA guideline recommends a flowchart to diagnose asthma (‘standard diagnostic work-up’) [1]. The first step in the diagnostic asthma work-up is to examine the detailed history of the patients. If the history supports asthma, spirometry with tested reversibility using a bronchodilator is recommended. Reversibility is demonstrated if the bronchodilatation test is positive (delta FEV1 ≥ 200 ml and ≥ 12%). The next step in the diagnostic procedure is the BPT to demonstrate bronchial hyperresponsiveness [1]. The BPT is considered positive if the FEV1 decreases by at least 20% following inhalation of ≤ 2.39 mg of histamine or ≤ 1.87 mg of methacholine. Approximately 60% of the patients with probable asthma has a positive BPT [5].

However, BPT is expensive, time-consuming, unpleasant for the patient, and can cause side effects [6]. In addition, most lung function departments in the Netherlands have limited capacity to perform all the needed BPTs resulting in delays in adequate diagnostic evaluation for the patient. Therefore, there is an urgent need for a new diagnostic asthma work-up to be implemented in asthma care.

Next to bronchial obstruction and hyperresponsiveness, bronchial wall inflammation also plays a role in asthma. Several inflammatory cells are involved in this process, such as lymphocytes, dendritic cells, mast cells, and eosinophils. Nitric oxide (NO) is associated with airway eosinophilic inflammation in asthma patients and can be measured in exhaled air with the FeNO-test [7].

The FeNO-test is currently not included in the diagnostic flowchart of the GINA guideline, as the BPT is still considered the gold standard [1]. Various studies show a sensitivity for FeNO between 85 and 88% and a specificity between 79 and 90% to diagnose asthma [2, 8]. In an appropriate clinical context and a FeNO above 50 ppb, the chance of a correct asthma diagnosis is 96% [8].

This study (Trial number: NCT06230458) investigates the value of the FeNO-test (cut off ≥ 50 ppb) as an add-on test, intending to determine the impact of the FeNO-based strategy, in terms of the number of avoided BPTs, cost-effectiveness, and reduced burden on the patient and healthcare. The FeNO-test can be used to rule in a diagnosis of asthma with confidence, however, the poor sensitivity does not allow asthma to be ruled out. Although the accuracy of the FeNO-test is extensively proven in previous studies, it is included for verification in this study.

The hypothesis is that the BPT will not be necessary for about 50% of the patients. This percentage will probably have a FeNO test result with a value of ≥ 50 ppb. These will be the patients with Type-2 high asthma (allergic/eosinophilic asthma). This type of asthma is the most common: about 50-70% of people with asthma have an underlying type 2 inflammation [9].

The UK National Institute for Health and Care Excellence (NICE) asthma guidelines recommend the use of the FeNO-test in the diagnostic asthma work-up [10]. Also, the ERS task force recommends the measurement of FeNO as part of the diagnostic work-up of children aged 5–16 years and adults with suspected asthma [2, 3].

The ultimate goal of this study is to implement the FeNO-test also in the GINA- and National asthma guidelines if this study demonstrates that incorporating the FeNO-test in the diagnostic work-up for asthma has favorable effects in terms of the number of avoided BPTs, cost-effectiveness, and reduced burden on the patient and healthcare.

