### Outcomes

The reduction in the number of provocation tests will be calculated by adding up the number of theoretically saved provocation tests. The decrease in direct and indirect costs will be calculated by adding up the costs of the number of provocation tests and the absence days, which were not necessary afterward, minus the extra costs of the FeNO measurement. The reduction in patient burden will be assessed with questionnaires. Asthma control and quality of life will be measured in the different groups using questionnaires. The accuracy of the FeNO test will be calculated by comparing the FeNO test results with the gold standard results of the challenge test.

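### The stated condition for guideline implementation (avoided BPTs, cost-effectiveness, burden) gives no role to agreement between FeNO and the BPT, and false positives count as avoided BPTs

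*Protocol article*

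**What the plan says.** All references are to the protocol article.

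- **Background.** The ultimate goal is implementation in the GINA and national guidelines if the new work-up "has favorable effects in terms of the number of avoided BPTs, cost-effectiveness, and reduced burden on the patient and healthcare". No threshold is attached to any of the three measures. On accuracy the section says: "Although the accuracy of the FeNO-test is extensively proven in previous studies, it is included for verification in this study".
- **Avoided BPTs.** Outcomes: "The reduction in the number of provocation tests will be calculated by adding up the number of theoretically saved provocation tests". The Background hypothesis is that about half of patients will not need the BPT, and it adds: "This percentage will probably have a FeNO test result with a value of ≥ 50 ppb". The Discussion makes the same link between a saved test and a FeNO of at least 50 ppb.
- **Costs.** Statistical analysis: the cost reduction is "established by the number of theoretically avoided BPT, theoretically avoided days of absenteeism caused by the BPT, and extra FeNO measurements". Misdiagnosis is not among the listed terms.
- **Burden.** Statistical analysis: the burden analysis consists of "calculating differences in VAS-score and AQLQ-score after the BPT and FeNO-test with an independent T-test".
- **Accuracy.** Statistical analysis: "The accuracy of the FeNO-test will be calculated by comparing the FeNO-test outcomes to the (gold standard) BPTs outcomes in terms of sensitivity and specificity". No minimum value is set and nothing links the result to the recommendation.
- **Limitation.** The Discussion names false-positive FeNO results as the limitation of the new approach and says the size of the affected group depends on the accuracy of the test.

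**The concern.** The new work-up would let patients with a high FeNO skip the reference test. That is defensible only if those who skip it would mostly have tested positive on the BPT. The study measures both tests in every patient, so it can answer this directly. Yet the condition for the main conclusion rests on a count of FeNO positives, a cost figure built from that count, and a comparison of how burdensome the two tests feel. None of these changes if the BPT results are shuffled among the patients.

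The article does not allow accuracy to be taken as settled. The Background cites sensitivity of 85–88% and specificity of 79–90%. The Discussion cites sensitivity of 0.19–0.81 and specificity of 0.75–0.95 at cut-offs above 40–50 ppb. The sample size uses specificity 0.85, while the Discussion assumes 90%. At stake is a guideline proposal whose stated condition cannot tell an informative FeNO from an uninformative one with the same positive rate.

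**Working it through.** **Inputs.** From Sample size calculation: prevalence 0.39, sensitivity 0.60, specificity 0.85, N = 171. From Ethics and dissemination: FeNO 5 min, BPT 70 min. The article gives no unit costs, so cost ratios below are assumptions.

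**1. Reproduce the plan's figure.** Share avoided = prevalence × sensitivity + (1 − prevalence) × (1 − specificity) = 0.39 × 0.60 + 0.61 × 0.15 = 0.2340 + 0.0915 = 0.3255. This is the stated 32.55%. With a full 95% CI width of 0.15, N = 1.96² × 0.3255 × 0.6745 / 0.075² = 149.9, the stated 150. The figure is reached only if the 9.15 points of false positives are counted as avoided BPTs, which confirms how the outcome is meant.

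**2. Two tests with the same positive rate, N = 171.**

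| | Planned FeNO (0.60 / 0.85) | Uninformative FeNO (0.3255 / 0.6745) |
|---|---|---|
| Avoided BPTs | 171 × 0.3255 = 55.7 | 55.7 |
| True positives | 171 × 0.39 × 0.60 = 40.0 | 171 × 0.39 × 0.3255 = 21.7 |
| False positives | 171 × 0.61 × 0.15 = 15.6 | 171 × 0.61 × 0.3255 = 34.0 |
| Positive predictive value (PPV) | 71.9% | 39% (the prevalence) |

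Net saving per patient = share avoided × (cost of BPT and absence) − cost of FeNO. It depends on the positive rate only, so it is the same in both columns.

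**3. Direction.** At sensitivity 0.60 the avoided share is 0.234 + 0.61 × 0.05 = 26.45% at specificity 0.95, 32.55% at 0.85, and 0.234 + 0.61 × 0.25 = 38.65% at 0.75. More false positives mean a better score.

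**4. How often would an uninformative test look favourable?** This depends on the bar. If the bar is any net saving, it is met when the observed positive share exceeds r, the ratio of FeNO cost to BPT cost. Exact binomial probabilities, N = 171:

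| r (assumed) | 32.55% positive | 15% positive |
|---|---|---|
| 1/14 (5 min / 70 min) | >0.999 | 0.999 |
| 0.10 | >0.999 | 0.96 |
| 0.15 | >0.999 | 0.50 |
| 0.20 | >0.999 | 0.03 |
| 0.30 | 0.75 | <0.001 |

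If the bar were the hypothesised 50%, a test with 32.55% positives would reach it with probability about 0.000001, accurate or not. Such a bar would not bring accuracy in either: at prevalence 0.39, even perfect sensitivity reaches 50% only with (0.50 − 0.39)/0.61 = 18% false positives among BPT-negative patients.

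**5. Which accuracy criterion works?** Simulated at N = 171, with BPT positivity of 0.39 (Sample size calculation) and of 0.60 (the approximate figure in the Background). LR+ = sensitivity / (1 − specificity). Its 95% CI uses the log scale, with variance 1/TP − 1/n₁ + 1/FP − 1/n₀, where n₁ and n₀ are the BPT-positive and BPT-negative counts. The PPV criterion uses the exact CI.

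| Sensitivity / specificity | Lower limit LR+ > 1, at 0.39; at 0.60 | Lower limit PPV > 0.50, at 0.39; at 0.60 |
|---|---|---|
| Uninformative 0.3255 / 0.6745 | 2.6%; 2.0% | <0.1%; 28% |
| Uninformative 0.15 / 0.85 | 2.4%; 1.7% | <0.1%; 12% |
| Informative 0.60 / 0.75 | >99%; >99% | 36%; >99% |
| Planned 0.60 / 0.85 | >99.9%; >99.9% | 90%; >99.9% |

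A fixed PPV limit behaves differently at the article's two positivity figures; the likelihood-ratio limit does not. Specificity alone is also insufficient: with about 104 BPT-negative patients, any test with specificity 0.85 has a lower limit (Wilson) above 0.75 with probability 0.71, including an uninformative one with 15% positives.

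**The case against.** The sentence in the Background is an ultimate goal, not a success criterion in the Methods, and it sets no threshold. A reader might infer that a worthless FeNO would pass almost every time. The article does not support that: the inference needs a bar of any saving above zero and assumed cost ratios, and it fails at a low positive rate with a costly FeNO, or at a 50% bar.

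Accuracy is also planned in the abstract, Outcomes and Statistical analysis. A reader might infer that the study would reach its favourable conclusion whatever the paired results show. That too goes beyond the text: a worthless test would show in the reported sensitivity and specificity, and the article does not say a failed verification would be ignored. The Background also cites a 96% chance of a correct diagnosis above 50 ppb, and FeNO is proposed for ruling in only, so wide variation in sensitivity says little about harm from skipped BPTs.

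Formal criteria and the content of cost-effectiveness may sit in documents not shown, and Outcomes does not define a saved test word for word.

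These points limit the claim but do not remove it. The article does state a condition, and that condition lists three measures without accuracy. The meaning of a saved test is fixed by the Background, the Discussion and the 32.55% arithmetic. The three-month follow-up does not fill the gap, because patients receive both FeNO and BPT results before diagnosis (Study design), so it does not show the outcome of a FeNO-only decision.

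**Conclusion.** The point holds in a limited form. As the article defines them, the three measures named in the implementation condition do not use FeNO–BPT agreement. At the planned inputs, 28% of avoided BPTs (15.6 of 55.7) would be false positives. For an uninformative test with the same positive rate it would be 61% (34.0 of 55.7), with the same avoided BPTs and the same costs. The counts rest on prevalence 0.39 and N = 171; the identity of the scores does not depend on either. No single probability of a false favourable conclusion can be given, because the threshold and unit costs are not stated. This should be corrected: it changes what the study can conclude, although the accuracy results would be there for readers to see.

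**What to change.** In the Background goal statement and in Statistical analysis, add to the condition a preset accuracy criterion from the paired data. Suggested wording: *A recommendation requires, in addition, that the lower limit of the two-sided 95% CI for the positive likelihood ratio of FeNO ≥ 50 ppb against the BPT exceeds 1.* This is a minimum that screens out an uninformative test; it does not by itself show that FeNO is good enough to replace the BPT. The investigators should choose any stricter limit for the likelihood ratio, or an added limit for specificity, before the data are analysed.

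Report avoided BPTs split into BPT-positive and BPT-negative patients, with the PPV and its exact 95% CI. If the criterion is not met, report avoided BPTs and costs without a recommendation.

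The cost is wording and two confidence intervals, with no extra patients, visits or tests. The small downside is that a favourable conclusion is no longer independent of accuracy; at the planned 0.60 / 0.85 the minimum criterion is met nearly always.
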